## Background

Type 2 diabetes mellitus is associated with an increased risk of dementia [1, 2] and more specifically, a two-fold increase in the risk of Alzheimer’s disease [3]. Many factors may contribute to this strong association, including increased stroke incidence, white matter microstructural changes, hyperinsulinaemia and metabolic syndrome, as well as the cross-association of mid-life obesity and type 2 diabetes [4]. A diagnosis of diabetes in midlife increases the risk of both vascular cognitive impairment and Alzheimer’s disease [5].

Magnetic resonance imaging (MRI) markers of structural brain aging such as reduced total brain volume, cortical thickness, hippocampal volume, and increasing white matter hyperintensity load, are correlated with performance on neuropsychological tests and are powerful predictors of dementia [6, 7]. A strong association between midlife vascular risk factors and structural brain aging has been demonstrated [8], although longitudinal brain volume changes have not been thoroughly examined in patients with type 2 diabetes. The PROSPER study findings suggested that elderly non-demented patients with type 2 diabetes had accelerated progression of brain atrophy compared to non-diabetic individuals and provided evidence for the hypothesis that diabetes exerts deleterious effects on neuronal integrity [9].

There is little evidence that intensive glycaemic management as reflected by lower HbA_1c_ levels in type 2 diabetes is associated with reduced dementia risk [10, 11] or cognitive decline [12]. The ACCORD-MIND study investigators [10] found no evidence that an intensive glycaemic treatment strategy targeting HbA_1c_ to <6% altered cognitive outcomes in patients with type 2 diabetes. However, the ACCORD study was halted due to higher mortality rates from cardiovascular events in the intensive arm [13]. Subsequent follow-up of the ACCORD-MIND participants found an association between poor cognitive function and the risk of severe hypoglycaemic events [14]. A further 80 months of follow-up in the ACCORDION MIND trial showed no long term benefits of intensive glycaemic control on cognition or brain MRI outcomes [15]. It therefore remains unclear if tight glycaemic control as reflected by lower HbA_1c_ levels lead to lower risk of dementia and better biomarkers are needed for the prediction of cognitive decline to stratify the risk of dementia in type 2 diabetes.

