Patients with type 2 diabetes have associated hypertension [16], a high prevalence of previously unknown heart failure [17] and left ventricular dysfunction [17, 18]. Left ventricular hypertrophy (LVH) is also highly prevalent in patients with type 2 diabetes [18] and hypertension [19] and is an established independent predictor of adverse cardiovascular outcomes, including stroke [20] and heart failure [21]. Patients with type 2 diabetes and co-morbid hypertension have increased left ventricular mass, more concentric left ventricular geometry, lower myocardial function, that is independent of age, sex, body size, arterial blood pressure and atherosclerosis, compared to hypertensive individuals without type 2 diabetes [16]. Diabetes and hypertension predispose to the ischemic small vessel disease underlying lacunar infarction. Lacunar infarction can result in cognitive decline from selective damage to frontal-subcortical circuits subserving processing speed and executive function, and these deficits are often observed in type 2 diabetes [22].

There is a strong association between cardiac disease and impairment across many cognitive domains, particularly in tests of executive function [23]. Heart failure is strongly associated with cognitive impairment [24–26] and is an independent risk factor for the development of Alzheimer’s disease and cerebrovascular disease [16]. Carotid atherosclerosis is associated with cognitive impairment [27], measures of structural brain aging [8] and reductions in parietal gray matter [8]. LVH is associated with progressive cognitive decline, independent of blood pressure and large artery stiffness [28]. Left ventricular mass is associated with worse performance on tests of both visuospatial and verbal memory [29], and there is a nonlinear association between left ventricular ejection fraction (EF) and measures of accelerated structural and cognitive brain aging [30].

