### D2 Study design

The D2 study is a single center, observational, longitudinal, case-control study. One hundred and sixty-eight adult patients, aged greater than 50 years with type 2 diabetes will be followed: 50% with LVH (case) and 50% without (control). Patients will be assessed at baseline (0 months) and will return for tests at the 24 month time-point. Based on recruitment in our other diabetes, cognitive and imaging trials, it is expected that 80–90 patients will be recruited annually for the first 2 years. Recruitment of new patients will be completed at the end of 2 years, allowing the next 2 years for follow-up.

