### Study outcome measures

Our primary endpoint is brain volume change at 2 years (hypothesis 1). Our co-primary outcome is the presence of cognitive decline at 2 years (hypothesis 2). We shall use advanced brain imaging to accurately measure brain volume and correlate this with cardiac echocardiography, carotid intima media thickness (CIMT), and 24 h blood pressure and ECG monitoring in 168 patients with type 2 diabetes, with longitudinal testing allowing measurement of change at 24 months. Concurrent neuropsychological testing will indicate whether the clinical profile of cognitive impairment and dementia aligns with measures of brain volume.

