#### Demographic and medical history questionnaire

A questionnaire and medical record review will be conducted at the time of the echocardiogram and blood collection. The following information will be collected: age, sex, duration of diabetes, smoking history, alcohol consumption, current drug therapy and dose, socioeconomic status family history of cardiovascular disease, medical history including general health and co-morbidities (cardiac disease, hypertension, dyslipidaemia, the presence of micro-vascular disease (nephropathy, retinopathy, neuropathy) and other macro-vascular complications (peripheral vascular disease). The questionnaire will be cross-checked by medical record review at Austin Health, and from their clinical and specialist reports if recruited outside of Austin Health.

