### Sample size

We aim to recruit 168 patients with type 2 diabetes. Patients will be divided based on the presence of LVH. Higher left ventricular mass and concentric geometric changes have been demonstrated in approximately 35–40% of patients with type 2 diabetes [16, 17]. Our data suggested more than 50% of participants will have LVH [18]. We calculated our sample size in order to include sufficient participant numbers for both the primary endpoint comparison (brain volume) and for the primary outcome measure (presence of cognitive impairment). The primary endpoint requires a direct comparison of two groups: type 2 diabetes patients with LVH and those without. We based our effect size on published brain volume and cortical thickness estimates performed on healthy controls, cerebrovascular disease patients and Alzheimer’s disease patients [40–42], and prior imaging of healthy controls and stroke patients performed by our group [43]. We use an average brain volume change of <0.5% per annum for controls, 1–2% for cerebrovascular disease, and 2–4% for dementia [44].

We used a modified retrospective case-control method. All participants have the exposure (type 2 diabetes), which will naturally halve by the additional risk factor (LVH, expected prevalence around 50%), but only some of them will develop the primary outcome (cognitive decline). We used an ANCOVA method to estimate sample size for four samples (cognitively impaired LVH, non-cognitively impaired LVH, cognitively impaired non-LVH, non-cognitively impaired non-LVH) with repeated measures, including a correlation score between baseline and follow-up. Using alpha = 0.05 (two-sided), power = 0.8 and an estimated correlation of 0.1, we estimated that 140 (i.e., 35 in each of 4 groups) participants will be required. Given we expect around 20% attrition due to death or non-participation (unable to participate in testing due to new pacemaker/implanted metal/other medical issue, lost to contact, no longer interested), we have estimated a total recruitment number of 168. This model has used the conservative estimates from these results and assumes the following: that 30% of patients will be cognitively impaired at 2 years; a 1% total annual brain volume change for patients with type 2 diabetes; that 30% of patients will exhibit specific left ventricular geometric changes; and a low correlation between baseline and follow-up measures.

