### Statistical analysis

The analysis of this study will be performed in three parts as follows.
***Hypothesis 1: comparing brain volumes between participants with and without LVH***. Independent samples t-tests will be used to determine differences between participants with and without LVH at each time-point. Repeated-measures t-tests will be used to determine the extent of brain volume loss across the two time-points. These results will be compared between groups. In the cortical thickness analyses, the large number of statistical inferences being carried out across the cortical sheet (approximately 160,000 vertices per hemisphere) requires adjustment of the statistical threshold. This is to control for the increased number of false positive findings using false discovery rate correction procedure widely used for cortical thickness analyses. In the volumetric analyses, total brain volume, regional white matter, cortical and subcortical volume changes will be modelled using a repeated measures design. Intracranial volume, which is determined partially by gender and race, is a known confounding factor that contributes to regional brain volumes. This will be controlled for in the statistical analysis of regional brain volume change. We have demonstrated this to be a reliable index of brain volume in previous studies [43].
***Hypothesis 2: correlating brain volume with cognitive performance.*** The initial regressive analysis will examine differences between cognitively impaired and normal participants at 2 years. We will correlate both global and regional measures of brain volume with the groups. Global brain and regional hippocampal volumes, and mean regional cortical thickness values for the stated regions of interest will be compared between two groups, in order to correlate LVH-associated brain volume changes with cognition. We will also perform a multivariate analysis across the cohort as a whole to investigate whether there is a dose-related association with any extent of cardiac impairment. Multivariate regression will be conducted to determine whether brain volume loss correlates with the presence or absence of cognitive impairment, adjusting for known important variables such as age, years of education, CIMT, atrial fibrillation, cholesterol and hypertension, as well as potentially relevant variables including *APOE* ε4 status, cardiac indices such as stroke volume, renal function and HbA_1c_ levels.

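### The primary LVH contrast on brain volume change names no covariate except intracranial volume (regional change only), so confounding by age or blood pressure can pass for an LVH effect

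*Protocol article*

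**What the plan says.** All references are to the Protocol article.

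- **Endpoint.** Study outcome measures: "Our primary endpoint is brain volume change at 2 years (hypothesis 1"). The Sample size section describes this endpoint as a direct two-group comparison, LVH against no LVH.
- **Design.** D2 Study design: "The D2 study is a single center, observational, longitudinal, case-control study". According to the Sample size section, the groups arise from the cohort itself, "which will naturally halve by the additional risk factor (LVH, expected prevalence around 50"%). No matching is stated.
- **Hypothesis 1 analysis.** Statistical analysis gives independent-samples t-tests at each time-point, and repeated-measures t-tests of volume loss whose results are then compared between groups. It also gives a repeated-measures model for total and regional volumes. Intracranial volume is identified as a confounder of regional volumes: "This will be controlled for in the statistical analysis of regional brain volume change". No other covariate is named.
- **Hypothesis 2 analysis.** A regression of brain volume loss against cognitive impairment, "adjusting for known important variables such as age, years of education, CIMT, atrial fibrillation, cholesterol and hypertension" and further variables.
- **Hypothesis 3 analysis.** Left ventricular structure and geometry are adjusted for age, sex, BMI and systolic blood pressure, with hypertension duration added. A multiple regression relates brain volume and cognition to higher left ventricular mass after allowing for established covariates and hypertension duration.
- **Data collected.** Demographic and medical history questionnaire: "The following information will be collected: age, sex, duration of diabetes, smoking history, alcohol consumption, current drug therapy and dose, socioeconomic status" and more. BMI, *APOE* genotype and 24-h ambulatory blood pressure are also measured.

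**The concern.** LVH status is not assigned, so the two groups can differ in anything that travels with LVH. The protocol supplies both links of a confounding path. On the exposure side: "Left ventricular hypertrophy (LVH) is also highly prevalent in patients with type 2 diabetes [18] and hypertension [19"]. On the outcome side: "A strong association between midlife vascular risk factors and structural brain aging has been demonstrated". Age belongs in the same argument, since the protocol treats it as an established covariate of left ventricular structure and as an important variable in the Hypothesis 2 regression.

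The study wants to say more than that LVH patients differ. The abstract asks whether LVH contributes to cognitive decline, and the Discussion presents a potentially treatable factor in the causation of cognitive impairment. If LVH patients are simply older or more hypertensive, the primary analysis could show greater atrophy in them with no contribution from LVH. Even for prediction, an LVH difference fully explained by age would add nothing to knowing the patient's age.

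**Working it through.** **1. Which stated analyses answer the primary question with adjustment?**

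| Analysis | Exposure or grouping | Outcome | Covariates named |
|---|---|---|---|
| Hypothesis 1 t-tests | LVH yes/no | Brain volume and its loss | None |
| Hypothesis 1 repeated-measures model | LVH yes/no | Total and regional volume change | Intracranial volume, for regional change |
| Hypothesis 2 regression | Cognitive impairment yes/no | Brain volume loss | Age, education, CIMT, atrial fibrillation, cholesterol, hypertension and others |
| Hypothesis 2 whole-cohort analysis | Extent of cardiac impairment | Dose-related association | None stated for it |
| Hypothesis 3 regression | Left ventricular mass | Brain volume and cognition | Established covariates, hypertension duration |

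No row has LVH yes/no as exposure, brain volume change as outcome, and adjustment for age, sex or blood pressure. Diabetes duration is collected but stands in no stated adjustment set.

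**2. Group size for an illustration.** The point rests on no figure in the plan. The plan's 140 evaluable patients cannot be recomputed, because no SD or standardised effect is given. Taking 140 and the expected LVH prevalence of about 50% gives 70 versus 70. At two-sided alpha 0.05 and power 0.80 the detectable difference is

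(1.960 + 0.842) × √(2/70) = 2.802 × 0.169 = 0.47 SD.

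With 20% loss from 168, 168 × 0.8 = 134.4, about 67 per group, and the detectable difference is 0.48 SD.

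**3. Spurious difference and false-positive rate.** Assume that LVH has no effect, that one confounder differs between groups by *s* SD, and that it correlates *r* with atrophy. The documents give neither *s* nor *r*. Then

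- spurious difference = r × s (in SD of atrophy);
- noncentrality λ = r × s / √(2/70);
- rejection probability = 1 − Φ(1.96 − λ) + Φ(−1.96 − λ).

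| r | s | Spurious difference (SD) | False-positive rate, unadjusted |
|---|---|---|---|
| 0.1 | 0.2 | 0.02 | 0.052 |
| 0.2 | 0.3 | 0.06 | 0.065 |
| 0.3 | 0.5 | 0.15 | 0.144 |
| 0.4 | 0.5 | 0.20 | 0.219 |
| 0.4 | 0.8 | 0.32 | 0.473 |

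Worked line: r = 0.3, s = 0.5 gives λ = 0.15/0.169 = 0.89, and the rate is 0.144. At 67 versus 67 the rates are almost the same (0.140 for that line, 0.212 for r = 0.4, s = 0.5).

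**4. Check by simulation.** With 5,000 runs per scenario at 70 versus 70, the unadjusted rates were 0.065, 0.137 and 0.217 for (r, s) = (0.2, 0.3), (0.3, 0.5) and (0.4, 0.5). With the confounder in the model they were 0.048, 0.048 and 0.049.

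**The case against.** The case for the plan has four parts.

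- **Hypothesis 1 is more than t-tests.** It includes a repeated-measures volume model, and a condensed article may leave that model's full covariate list to an analysis plan. This stands in so far as nobody should read the article as excluding age or blood pressure. It does not remove the point: the article raises confounding within Hypothesis 1, names intracranial volume and stops, while giving covariates for Hypotheses 2 and 3.
- **An adjusted analysis of nearly the same exposure exists.** LVH is defined as a cut-off on indexed left ventricular mass, and the Hypothesis 3 regression relates brain volume to that mass with adjustment. This is real mitigation. But it is not the primary contrast, it does not name diabetes duration, and nothing says which result governs if the two disagree.
- **LVH may be meant only as a marker.** An unadjusted difference is a legitimate description for that purpose, and parts of the Background read that way. The contributory and causal wording in the abstract and Discussion goes further.
- **Blood pressure may lie on the pathway.** Adjusting for it could then remove part of the effect of interest. This stands and shapes the fix.

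A reader might also infer that years of education and duration of hypertension are not collected, because the questionnaire section does not list them. The documents do not support that. The section summarises a form that is not shown, records are cross-checked, and the plan to adjust for both implies that they are recorded.

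**Conclusion.** The concern holds for the primary Hypothesis 1 contrast. As written, its only named covariate is intracranial volume, and that only for regional change, in unmatched observational groups for which the protocol itself describes the confounding path. The Hypothesis 3 regression on left ventricular mass reduces the problem without resolving it.

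The size is illustrative only. Moderate confounding (s = 0.5, r = 0.3 to 0.4) would give a spurious difference of 0.15 to 0.20 SD, against a detectable 0.47 SD, and a false-positive rate of about 14–22% instead of 5%. Weak confounding leaves the rate near 5%. These figures assume a single confounder, a linear relation and no true LVH effect. The return to 5% after adjustment also assumes that the confounder is measured and included.

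Two stronger readings are tempting and not supported. One is that the plan has no adjusted analysis of brain volume against cardiac structure; it has one, under Hypothesis 3. The other is that the primary result will be confounded by a known amount, for example at the high end of the table; the documents give neither the imbalance nor the correlation.

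**What to change.** Make the confirmatory Hypothesis 1 estimate the LVH coefficient from a prespecified model of brain volume change, adjusted for baseline covariates already collected: age, sex, intracranial volume, BMI and diabetes duration, with *APOE* ε4 optional. Report the t-test difference alongside as descriptive.

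For blood pressure, name one version in advance as confirmatory, either with or without 24-h systolic pressure (or hypertension), and report the other as a sensitivity analysis. State that the Hypothesis 3 regression on left ventricular mass is supportive.

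The cost is analysis wording and a few degrees of freedom: five for the core set, up to seven with blood pressure and *APOE* ε4 (each as one term), out of roughly 134 to 140 evaluable patients. No new data and no change in sample size are needed. Fixing the model before outcome data are examined also avoids choosing covariates after the fact.

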***Hypothesis 3: comparing brain volume and cognitive performance in participants with increased left ventricular mass and specific left ventricular geometric patterns.*** Analysis will be similar to that for LVH, except that patients will be divided on the presence or absence of specific morphometric measures. That is, analyses will be performed at each time-point (cross-sectional), and also longitudinally, to investigate change across time. Repeated-measures t-tests will determine the extent of brain volume loss across the two time-points and compared between groups. Correlation with cognitive performance will be performed as above. Unadjusted differences for clinical variables between groups will be assessed by *t*-test. Difference in laboratory data and left ventricular systolic function will be adjusted for age and sex by use of ANCOVA. Differences in left ventricular structure and geometry will be adjusted for age, sex, BMI, and systolic blood pressure as their major established covariates with further adjustment for duration of hypertension. Fisher’s Exact Test and odds ratios will be used to test differences for categorical variables. Logistic regression analysis will be used to derive odds ratios adjusted for covariates. Multiple regression analyses will be performed to assess relation of cognitive and brain volume measures to higher left ventricular mass independent of established covariates and duration of hypertension.

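### Intracranial volume is named as a confounder but controlled only for regional change, so the LVH comparisons of brain volume at each time-point are unadjusted, imprecise and open to confounding by head size

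*Protocol article*

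**What the plan says.** All of this is in the Statistical analysis section of the protocol article unless noted.

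- **Time-point comparisons (Hypothesis 1).** "Independent samples t-tests will be used to determine differences between participants with and without LVH at each time-point".
- **Change (Hypothesis 1).** "Repeated-measures t-tests will be used to determine the extent of brain volume loss across the two time-points", with the results then compared between groups. For volumetry, "total brain volume, regional white matter, cortical and subcortical volume changes will be modelled using a repeated measures design".
- **Status of ICV.** "Intracranial volume, which is determined partially by gender and race, is a known confounding factor that contributes to regional brain volumes".
- **Scope of the control.** "This will be controlled for in the statistical analysis of regional brain volume change". The section nowhere extends ICV adjustment, or scaling of volumes to ICV, to total volume or to the time-point comparisons.
- **Hypothesis 2.** "Global brain and regional hippocampal volumes, and mean regional cortical thickness values for the stated regions of interest will be compared between two groups". The two groups here are cognitively impaired and normal participants at 2 years. ICV is not mentioned.
- **Hypothesis 3.** The analysis follows that for LVH, with groups formed by ventricular morphometry: "analyses will be performed at each time-point (cross-sectional), and also longitudinally, to investigate change across time".
- **How the groups arise (Sample size).** "Patients will be divided based on the presence of LVH". LVH status is observed, and no matching is described.

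**The concern.** Head size matters most when different people are compared at one time-point. A larger head holds a larger brain, so raw volume mixes atrophy with head size. Head size matters least in within-person change, where it largely cancels. The article states ICV control for the second kind of analysis and names an unadjusted test for the first.

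Two things are at stake. First, precision: variation in volume that is due to head size stays in the error term of the t-test and can hide a real difference between LVH groups. This holds even when the groups have identical head-size distributions. Second, bias: the groups are not randomised. If they differ in ICV, for instance through sex or ancestry, a smaller mean brain volume in one group could be read as atrophy when it reflects head size. The baseline comparison will also be the first result available from the study.

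**Working it through.** The article gives no SD of brain volume, no ICV-volume correlation and no sex or ICV distribution by LVH group. The article's figures and the assumptions are therefore kept apart.

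**Inputs from the article (Sample size).** Two-sided alpha 0.05; power 0.80; 140 evaluable; LVH prevalence around 50%, so 140/2 = 70 per group at 24 months. At baseline, 168/2 = 84 per group.

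**Assumed inputs.** Correlation r between ICV and brain volume within groups: 0.8 to 0.9. Standardised group difference in ICV, D: 0, or 0.1 to 0.3 SD.

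**Step 1: precision, no imbalance needed.** A two-sided 5% t-test with 70 per group has 80% power at a difference of 0.477 SD of raw volume. With ICV as a covariate, the residual SD is multiplied by √(1 − r²):

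- r = 0.8: 0.477 × √(1 − 0.64) = 0.477 × 0.600 = 0.286 SD
- r = 0.9: 0.477 × √(1 − 0.81) = 0.477 × 0.436 = 0.208 SD

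**Step 2: bias if ICV differs.** With no true LVH effect, the expected raw difference is r × D in SD units. The non-centrality of the t-test is r × D × √(n/2), and √(70/2) = 5.916.

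| r | D | Bias (SD) | Non-centrality | Rejection rate, 70 v 70 |
|---|---|---|---|---|
| either | 0 | 0 | 0 | 5.0% |
| 0.8 | 0.1 | 0.08 | 0.473 | 7.6% |
| 0.9 | 0.3 | 0.27 | 1.597 | 35.4% |

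At baseline with 84 per group, the same two non-zero cases give 8.1% and 41.3%.

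**Step 3: a second route, through sex imbalance.** This was a simulation with 70 per group, 4000 replicates and no LVH effect. Its assumptions were a 10% sex gap in brain volume, a within-sex ICV SD of 8% and a within-sex ICV-volume correlation of 0.9.

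| Male share, LVH / non-LVH | Plain t-test at one time-point | With ICV as covariate | t-test on 24-month absolute change |
|---|---|---|---|
| 50/50 | 5.3% | 5.6% | 4.6% |
| 55/45 | 9.3% | 5.3% | 5.6% |
| 60/40 | 22% | 5.0% | 5.7% |
| 65/35 | 42% | 5.4% | 6.3% |

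The last column shows why the primary endpoint is largely spared: the change contrast stays near 5% even where the time-point test does not.

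**Step 4: scale against the article's own rates.** The Sample size section assumes 1% annual volume change in type 2 diabetes and under 0.5% in controls. Taking 0.5% for controls, the gap is (1 − 0.5) × 2 = 1 percentage point at 24 months. That is not a stated LVH effect, only a benchmark. An assumed sex gap of 8 to 12% with a 10-point difference in male share shifts a raw cross-sectional mean by 0.8 to 1.2%, about the same size.

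**The case against.** The strongest reply has five parts.

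1. **The primary endpoint is change.** Correct, and it limits the point. A reader might infer that the main test of Hypothesis 1 is confounded by head size. The document does not support that: the outcome measures section defines the primary endpoint as change at 2 years, and Step 3 shows head size largely cancelling there.
2. **No imbalance is shown.** Also correct. The article gives no sex, height or ICV figures by LVH group. A reader might take the sex-specific LVH cut-offs and the indexing by height^2.7 as signs that head size will differ. They are no evidence of that, since such indexing is meant to take body size and sex out of the classification. The t-tests are therefore open to confounding, which is not the same as shown to be confounded. The precision loss in Step 1 does not depend on this.
3. **The volumes may be scaled to ICV beforehand, or the full analysis plan may add the adjustment.** This is possible, and the article does not say that ICV will be ignored elsewhere. But it is not merely silent: it names the test, names the confounder and states where the confounder will be controlled. Read as written, the time-point tests are unadjusted.
4. **Hypothesis 2 is described as a regression-type analysis with an open-ended covariate list.** This stands. The list serves a model of volume loss, and leaving ICV and sex off an open list does not exclude them. A reader might infer that Hypothesis 2 has ruled out ICV; it has not. What is left is a clarification for the comparison of impaired and normal participants' volumes.
5. **Hypothesis 3 already plans some adjusted regression.** It does relate brain volume measures to ventricular mass with adjustment for established covariates. ICV is not named there, and the cross-sectional group comparisons still follow the t-test pattern of Hypothesis 1.

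**Conclusion.** The point holds for the cross-sectional comparisons of brain volume by LVH status at baseline and 24 months, and for the matching comparisons by ventricular geometry under Hypothesis 3. The article identifies a confounder and applies its remedy where it matters least, while fixing a test that cannot use it where it matters most.

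On an assumed ICV-volume correlation of 0.8 to 0.9, the unadjusted test with 70 per group detects 0.48 SD, where an adjusted one detects 0.21 to 0.29 SD. This loss occurs with or without imbalance. The false-positive rate stays at 5% if ICV does not differ between groups, and reaches about 8 to 35% only if it differs by an assumed 0.1 to 0.3 SD. The second range follows from the chosen inputs and is no forecast for this cohort. The primary contrast in 24-month change is largely unaffected, and no sample-size figure changes. This is a worthwhile correction to supporting analyses and does not threaten the main result.

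**What to change.** - For Hypotheses 1 and 3, replace the time-point t-tests on total, regional and hippocampal volume with ANCOVA on group, ICV, age and sex.
- Take ICV from the T1 structural scan and FreeSurfer processing already planned.
- State that ICV control covers total and hippocampal as well as regional volumes, and the time-point comparisons as well as change.
- For Hypothesis 2, state that ICV is a covariate when the volumes of cognitively impaired and normal participants are compared at 2 years.
- Leave the contrast in 24-month change as the primary test, as planned.

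The cost is analysis wording. No further scan, visit or participant is needed. If the volumes are already to be scaled to ICV before testing, one sentence saying so would answer most of the point.
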